### Statistical analysis

Data will be analyzed using SPSS19.0 software (IBM Corp., Armonk, NY, USA). A statistical significance level of 0.05 will be used. Normally distributed data will be expressed as the mean ± standard deviation, and non-normally distributed data will be expressed as the median, minimum, and maximum. Classified variables will be expressed as a number and percentage.

The analysis will be performed on the basis of the intent-to-treat principle. A full analysis set following the principle of intent-to-treat will consist of a data set for all patients who participated in the trial, regardless of compliance or withdrawal. For patients who are lost to follow-up, the missing data will be imputed by the last-observation-carried-forward method based on the final observed value.

Descriptive statistics will be used for baseline feature data. Pearson’s chi-squared test or Fisher’s exact test will be used for intergroup comparisons of categorical variables, such as curative outcomes and postoperative incidence of adverse events. For independent variables, such as IKDC score, VAS score, T2 value, and △*R1*, an independent sample *t* test or the Mann-Whitney *U* test will be used.

A multivariate logistic regression analysis model will be used to adjust for possible confounding variables such as age, sex, etiology, cartilage defect area, meniscus injury, course of disease, severity of cartilage injury, postoperative complications, and surgeon (experience).

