#### Definitions

##### Adverse events

Adverse medical events may occur after cartilage transplantation or microfracture surgery, but they do not necessarily have a causal relationship with treatment (Table 1).

**Table 1 Tab1:** Adverse event registration form

Adverse events		Appearance time	Duration
Fever	□		
Joint pain	□		
Joint snapping	□		
Joint noose	□		
Joint swelling	□		
Activity limitation	□		
Pruritus	□		

Common adverse reactions after cartilage transplantation include fever, joint pain, swelling, and effusion. Common adverse reactions after microfracture surgery include fever, joint pain, joint swelling, and effusion.

Adverse events will be relieved by nursing care, such as reducing activity, intermittent ice compress, and the use of non-steroidal anti-inflammatory analgesic drugs.

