### Withdrawal criteria

Patients can withdraw from the study for any of the following reasons: severe adverse events (such as postoperative infections that are not eased within 1 week after surgery) related to the research; severe complications or rejection; the patient is asked to withdraw from the trial; considering the security or the benefit of the patient, the researchers believe that the patient is no longer suitable for continuing clinical validation; the patient fails to meet surgical requirements under arthroscopy; or is lost to follow-up. The time and cause of withdrawal will be recorded on an electronic Case Report Form (eCRF) in detail. When the study is discontinued, the patient should be assessed at the final visit except for those lost to follow-up. Free strategies for referral, physical examination, and MRI review will be conducted during the trial to improve patient compliance.

For patients who are out of the group and cannot be replaced or re-enter the clinical trial, their data will be treated as follows: (1) all source data and source files related to all withdrawn participants will be retained for retention and intent-to-treat analysis. After withdrawal, the researchers will attempt to contact the patient by telephone or mail to ask the reasons for withdrawal; (2) the time and cause of withdrawal will be recorded in the eCRF in detail; and (3) if there is judged to be a causal relationship with the trial, withdrawal due to adverse events will be recorded in the eCRF and the sponsor will be notified. For such patients, follow-up will be conducted until adverse events are resolved or stabilized.

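### Adverse event incidence is placed on the intent-to-treat set with carry-forward, which can dilute graft-specific harms by up to the share of patients never grafted

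*Protocol article*

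**What the plan says.** The rules are all in the protocol's *Statistical analysis* section:

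- Principle: "The analysis will be performed on the basis of the intent-to-treat principle".
- Analysis set: one is named, the full analysis set, which "will consist of a data set for all patients who participated in the trial, regardless of compliance or withdrawal".
- Test: Pearson's chi-squared or Fisher's exact test "will be used for intergroup comparisons of categorical variables, such as curative outcomes and postoperative incidence of adverse events".
- Missing data: for patients lost to follow-up, "the missing data will be imputed by the last-observation-carried-forward method based on the final observed value".
- Level: "A statistical significance level of 0.05 will be used".

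No set of operated or grafted patients is named, and neither the intent-to-treat rule nor LOCF is limited to efficacy.

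Other sections show who can be in that set. Under *Interventions in the experimental group*, treatment takes two operations. The first is an arthroscopy that assesses whether treatment can go ahead and, if so, harvests cartilage. Cells are cultured for 3–4 weeks, and the graft is implanted at the second operation. *Withdrawal criteria* lists among the reasons that "the patient fails to meet surgical requirements under arthroscopy; or is lost to follow-up", and keeps withdrawn patients' data for the intent-to-treat analysis. The control arm has one operation. *Study objectives* makes the comparison of safety a secondary objective.

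**The concern.** Intent-to-treat guards the efficacy comparison, but for harms it does not err on the cautious side. An event that needs the graft, such as rejection, cannot occur in a patient who never reached the second operation. Keeping that patient in the denominator lowers the incidence of such events. Non-receipt through the gap between two operations is possible only in the experimental arm, so for these events the effect runs in the graft's favour.

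Two further features suit harms badly. LOCF, applied to a patient lost without an event, carries the absence of an event forward to visits that did not take place. A crude proportion also gives a patient seen for 3 months the same weight as one seen for 18. At stake is how the safety results of a newly developed implant are read, including a finding of no difference.

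**Working it through.** **Plan's own figure.** The protocol states no adverse event rate and no never-grafted share, so there is no figure to reproduce. The only anchors are 50 patients per arm and a predicted dropout of 20% (*Sample size*). That 20% covers the whole trial and all reasons for leaving, so it serves here only as an upper end. Event risks and never-grafted shares below are assumptions.

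**1. Events that need the graft.** Let p be the risk among grafted patients and f the share of the experimental arm never grafted but kept in the denominator. Reported incidence = p × (1 − f), a relative reduction of exactly f.

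| f | never grafted, of 50 | p = 10% reported as | p = 30% reported as |
|---|---|---|---|
| 5% | 2.5 | 9.5% | 28.5% |
| 10% | 5 | 9% | 27% |
| 20% | 10 | 8% | 24% |

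**2. Adverse events overall.** Ungrafted patients who had the first operation carry some risk q from it. Reported incidence = (1 − f)p + fq, and the shortfall is f(p − q). With p = 30% and f = 20%:

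- q = 0: 24%, a shortfall of 6 points
- q = 10%: 0.24 + 0.02 = 26%, a shortfall of 4 points
- q = 20%: 0.24 + 0.04 = 28%, a shortfall of 2 points

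Setting q = 0 is therefore the upper bound.

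**3. Chance of showing an excess, at that upper bound.** Assume 30% among grafted patients, 10% in controls, all 50 controls treated and q = 0. Approximate power = Φ[(d − 1.96 × SE0) / SE1], with d the difference in risk, SE0 from the pooled proportion and SE1 from the separate ones. At f = 10%:

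- Full set, 50 v 50, 27% v 10%: d = 0.17, SE0 = √(0.185 × 0.815 × 2/50) = 0.0777, SE1 = √(0.27 × 0.73/50 + 0.10 × 0.90/50) = 0.0758; power 59%.
- Grafted only, 45 v 50, 30% v 10%: d = 0.20, SE0 = 0.0814, SE1 = 0.0804; power 69%.

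At f = 5% the pair is 65% and 70%; at f = 20% it is 46% and 67%. Exact enumeration of the chi-squared test gives 62% and 71% at f = 10%, and 49% and 67% at f = 20%. If instead the true risk is 30% in both arms, the graft looks 1.5, 3 or 6 points safer at f = 5%, 10% or 20%.

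**4. Early leaving.** Suppose 20% leave each arm and all are counted event-free, which is the extreme case. Then 30% v 10% becomes 24% v 8%: the ratio stays at 3 and the difference falls from 20 to 16 points. Events seen before leaving are kept, so the real effect is smaller. For example, take a 40% risk over 18 months at constant hazard (−ln 0.6 = 0.511), with 20% leaving uniformly over follow-up. Leavers have an average observed risk of 1 − 0.4/0.511 = 0.217, and the crude incidence is 0.8 × 0.40 + 0.2 × 0.217 = 36.3%. With equal leaving, this happens in both arms.

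**The case against.** The strongest reply is that the damaging step is not written down. A reader might infer that the plan counts ungrafted and early-leaving patients as event-free, and so under-reports the graft's harms. The documents do not support that as a statement of fact:

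- No sentence says such patients count as event-free. LOCF applies to patients lost to follow-up and to a final observed value. Adverse events are assessed at postoperative visits, so a patient never operated on has no such observation to carry forward.
- Participation in the trial is not defined, and a postoperative incidence could be read as having an operated denominator.
- Eligibility requires arthroscopic diagnosis, and eligible patients are then randomised, so some arthroscopic failures may fall before randomisation. That withdrawal reason is not limited to the experimental arm either.
- The first operation includes debridement and, where requirements are met, harvest. Fever, pain, swelling and effusion can follow it.
- Adverse events are collected to the end of the study, and patients withdrawn for trial-related events are followed until resolution or stabilisation.
- Comparing harms by randomised strategy is a legitimate answer to the safety objective, and a safety set may stand in an analysis plan that is not shown.

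These points limit the size and certainty of the concern. They do not remove it. The protocol is not silent: it states one basis for the analysis and lists adverse event incidence under it, so a safety set defined elsewhere would depart from this text. *Withdrawal criteria* treats failure at arthroscopy as leaving the trial, and the experimental intervention itself contains such an assessment, so non-receipt of the graft after enrolment is foreseen.

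**Conclusion.** The concern holds in conditional form. The stated basis for comparing harms suits them badly: a single intent-to-treat set, LOCF without a safety exception, and a crude proportion. If patients never grafted stay in the denominator, graft-specific incidence is diluted by up to the never-grafted share, which is a relative 5–20% over the assumed range. For adverse events overall the dilution is smaller, by an amount that depends on the unknown risk of the first operation. The power losses shown are upper bounds, because they set that risk to zero and treat every control as operated.

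It would go too far to say that the graft will be reported as safer than it is. Neither the event rates nor the never-grafted share is given, and the 20% dropout cannot be read as the never-grafted share. Early leaving does not by itself favour the graft, and a treated-patient set would not cure it; that part needs follow-up time to be taken into account.

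**What to change.** In *Statistical analysis*:

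1. Keep intent-to-treat for efficacy.
2. Analyse adverse events in all patients who underwent at least one study operation. Keep harvest-only patients and their events in the experimental-strategy comparison, so that harms of the first operation, including any that prevented the graft, are not moved out of sight.
3. In addition, report post-transplant events per patient transplanted. This gives the undiluted incidence of graft-specific events, which step 2 alone does not.
4. State that LOCF is not applied to adverse events.
5. Report cumulative incidence or time to first event, censored at last contact, with the starting point of each analysis stated. The Table 1 form already has an appearance time, and *Recording and reporting* asks for the time of occurrence of every event.

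The cost is a paragraph of text and one extra set of tables, with no new data or patients. The drawback is that the per-transplanted rates are not a randomised comparison and should be labelled so.

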**Methods:**

This is a prospective randomized controlled trial. One hundred patients with full-thickness cartilage injury of the knee will be randomly divided into two groups to receive treatment with either tissue-engineered cartilage constructed using biomimetic cartilage extracellular-matrix-oriented scaffolds combined with autologous chondrocytes, or arthroscopic debridement and microfracture surgery. There will be five visiting time points: at baseline, then at 3, 6, 12, and 18 months postoperatively. The primary outcome will be therapeutic efficacy as assessed by the Lysholm score at 12 months postoperatively. The secondary outcomes will be the International Knee Documentation Committee score, Visual Analog Scale score, and cartilage injury and repair as assessed by magnetic resonance imaging as well as the incidence of postoperative adverse events.

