### Outcome measures

#### Primary outcome measure

The Lysholm score for efficacy evaluation will be recorded at 12 months postoperatively. The Lysholm score [22] ranges from 0–100 points and consists of eight dimensions: a score of 80–100 points indicates elimination of all or the main symptoms, basic recovery of joint function, being capable of participating in normal labor and work (excellent); 60–79 points indicates elimination of all or the main symptoms, basic recovery or great improvement in the main function of the joint (good); and 0–59 points indicates no symptom improvement or symptom deterioration (poor). Efficiency = the number of excellent and good cases/the total number of cases × 100%.

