### Sample size

Based on our previous experience [25] and pilot study results, we assumed that the therapeutic efficiency on full-thickness cartilage injury of the knee joint would be 78% for microfracture surgery and 97% for autologous, cell-derived, tissue-engineered cartilage transplantation. Considering *α* = 0.05 (two-sided), and power = 80%, the necessary sample size was calculated as *n* = 84. With a predicted dropout rate of 20%, the required sample size was calculated as *n* = 50 per group.

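### Last observation carried forward is the only stated rule for missing scores, so earlier Lysholm scores can count as 12-month results and bias the comparison in either direction

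*Protocol article*

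**What the plan says.** The primary outcome section of the protocol article fixes one time point: "The Lysholm score for efficacy evaluation will be recorded at 12 months postoperatively". It then converts the score to a responder rate, with 60 points or more counting as excellent or good: "Efficiency = the number of excellent and good cases/the total number of cases". The sample size is built on that rate, which it assumes "would be 78% for microfracture surgery and 97% for autologous, cell-derived, tissue-engineered cartilage transplantation".

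Visits are scheduled "at baseline, then at 3, 6, 12, and 18 months postoperatively", so the only scheduled scores before month 12 are those at baseline, month 3 and month 6.

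The Statistical analysis section keeps every participant in the full analysis set, including those who withdraw. For patients lost to follow-up, "the missing data will be imputed by the last-observation-carried-forward method based on the final observed value". No other missing-data rule is given. The Sample size section expects loss: "With a predicted dropout rate of 20"%.

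The Withdrawal criteria list reasons that can be linked to treatment and outcome. Two adjacent entries read "severe complications or rejection; the patient is asked to withdraw from the trial"; others are related severe adverse events, failing the surgical requirements at arthroscopy, and loss to follow-up. The same section asks for an assessment at the final visit on discontinuation, except for those lost to follow-up. It also follows patients withdrawn for trial-related adverse events until the event resolves or stabilises.

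**The concern.** Knee function is expected to change during the year after surgery. Carrying forward assumes that it does not, and treats the substituted score as if it had been observed at month 12.

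The error can run both ways. A patient lost early, while still recovering, may be counted as a failure although the knee would have reached 60 by month 12. A patient who scores 70 at month 6 and is then lost because the repair failed is counted as effective.

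Nothing in the article supports assuming that these errors cancel between arms. The experimental arm has two operations with a 3 to 4 week cell culture between them, so there is an extra interval in which to lose a patient who has only a baseline score. Rejection is named after cartilage transplantation but not among the common events after microfracture. Patients know their allocation. The primary comparison could therefore depend partly on the timing and reasons of loss.

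**Working it through.** **Inputs from the article.** 50 patients per arm; responder rates 78% and 97%; "0.05 (two-sided), and power = 80"%; dropout 20%, so 0.20 × 50 = 10 patients per arm; Pearson chi-squared or Fisher's exact test.

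**Inputs assumed.** The share of carried scores at 60 or above in each arm (q), and any imbalance in loss. The article gives neither, so everything below is illustration.

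**The plan's own figure.** The stated total of 84 was not reproduced: standard two-proportion formulas at these settings give 80 (arcsine), 88 (unpooled) and 94 (pooled). That is a separate matter. Nothing below uses 84.

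**Formula.** With response rate p in an arm, loss d and carried response rate q, the analysed rate is (1 − d) × p + d × q. The stated rates 78% and 97% are taken as p. Power is obtained by enumerating all outcomes for two binomials, using Fisher's test when an expected count is below 5 and Pearson's otherwise.

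**Reference values.** With all 50 per arm observed, power is 85.6%. With 40 observed per arm and nothing imputed, it is 70.5%. The second is the fair comparator, because the plan expects to lose 20%.

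**True rates 78% and 97%, 20% loss in each arm**

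| Carried rate, control / experimental | Analysed rates | Difference (points) | Power |
|---|---|---|---|
| 75% / 75% | 77.4% vs 92.6% | 15.2 | 59.8% |
| 50% / 50% | 72.4% vs 87.6% | 15.2 | 49.0% |
| 0% / 0% | 62.4% vs 77.6% | 15.2 | 38.2% |
| 70% / 90% | 76.4% vs 95.6% | 19.2 | 83.5% |

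First row worked: 0.8 × 0.78 + 0.2 × 0.75 = 0.774, and 0.8 × 0.97 + 0.2 × 0.75 = 0.926. Whenever the carried rate is the same in both arms, the difference shrinks to 0.8 × 19 = 15.2 points. When carried rates follow the arm, as in the last row, it need not shrink.

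The direction is open. Carried rates of 50% (control) and 97% (experimental) give a 24.6-point difference; 97% and 50% give 5.8 points.

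**No true difference, 78% in both arms**

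| Loss, control / experimental | Carried rate, control / experimental | Analysed rates | Rejection rate |
|---|---|---|---|
| 20% / 20% | 0% / 0% | 62.4% vs 62.4% | 5.1% |
| 15% / 25% | 0% / 0% | 66.3% vs 58.5% | 12.8% |
| 20% / 20% | 30% / 80% | 68.4% vs 78.4% | 20.5% |

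Error is controlled when loss and carried rates are both equal between arms. It is not controlled when either differs, unless the differences happen to offset.

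**The case against.** The strongest reply is that the withdrawal section is better than it may first appear. A reader might infer that patients withdrawn for rejection or complications leave follow-up, so that a good score from before the failure is carried to month 12. The document does not support that. It asks for an assessment on discontinuation and follows trial-related adverse-event withdrawals until resolution or stabilisation, so the last value may well record the failure. The carrying-forward sentence also names only patients lost to follow-up; extending it to other withdrawals is an inference. This part of the objection stands, and carry-over of a score from before failure applies mainly to patients who are lost.

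A second reply concerns the scenarios. Measuring the power loss from 85.6% would be unfair, since 15.1 points of it (85.6 − 70.5) come from having fewer patients. The 12.8% figure needs unequal loss and every carried score below 60. With every carried score below 60, carrying forward is the same as counting each dropout as a failure, so that inflation is not peculiar to this method. With carried rates of 70% and 90%, power exceeds that of the 40 observed alone. All of this is correct, and it is why the figures are a range under assumptions.

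What the objection does not remove is that the article nowhere says a 12-month Lysholm score is obtained after withdrawal. The final visit could mean an exit visit or the scheduled last visit, and following an event to resolution does not supply a month-12 score. If the rule does not cover other withdrawals, the full analysis set includes them with no stated value. Nor is this a detail left to an unseen analysis plan, because the article itself fixes the method.

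**Conclusion.** The concern holds in a limited form. The one stated missing-data rule puts an earlier score in place of the 12-month result for patients lost to follow-up (baseline only for a patient lost before the second surgery), in a trial that expects to lose about a fifth of its patients. The resulting bias can favour either arm.

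Its size cannot be fixed from the documents. Under the assumed carried rates tabulated, power runs from 38% to 83.5% against 70.5% for 40 observed per arm, and the false-positive rate from about 5% to about 20%. It would go too far to conclude that the plan favours the experimental treatment, or that the false-positive rate is inflated as a matter of course: the first needs knowledge of who is lost and why, and the second fails when loss and carried rates are equal. This should be fixed, but it does not by itself invalidate the design.

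**What to change.** In Statistical analysis, make multiple imputation of the Lysholm score the primary missing-data method, done separately by arm from baseline and all visits, and derive the responder rate (60 or more) from the imputed scores. This keeps the endpoint on which the trial was sized. Keep carrying forward as a sensitivity analysis.

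Multiple imputation assumes that data are missing at random, so it does not by itself correct for a patient who is lost because the repair failed. Add a sensitivity analysis that counts withdrawals for rejection or severe complications as not effective.

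In Withdrawal criteria, state that the 12- and 18-month outcome assessments continue after withdrawal unless the patient withdraws consent, and define the final visit.

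The cost is revised wording in two sections, more analysis work and some extra follow-up effort. The imputation uses visits already scheduled.

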### Study design

This prospective, single-blind, randomized controlled clinical trial will be conducted at the Institute of Orthopaedics, Chinese PLA General Hospital, China. The study design is compliant with the Standard Protocol Items: Recommendations for Interventional Trials (SPIRIT) Statement [20] (see Additional file 1). After providing informed consent, the potential patients with full-thickness cartilage injury of the knee joint will be screened according to the inclusion and exclusion criteria, and finally, 100 eligible patients will be randomly assigned to receive autologous-cell-derived tissue-engineered cartilage grafts (*n* = 50) or microfractures (*n* = 50). The primary outcome is therapeutic efficacy as assessed by the Lysholm score at 12 months postoperatively. The secondary outcomes are the IKDC score, Visual Analog Scale (VAS) score, and cartilage injury and repair as assessed by MRI as well as the incidence of postoperative adverse events (see the trial flow chart in Fig. 3). The Standard Protocol Items: Recommendations for Interventional Trials (SPIRIT) Figure is detailed in Fig. 4.

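### The primary 12-month Lysholm efficacy rate is tested without adjustment for the baseline Lysholm score that the trial collects; the test is valid, but some efficiency may be given up

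*Protocol article*

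**What the plan says.** Under Primary outcome measure, the article bands the 12-month Lysholm score and defines an efficiency rate: patients rated excellent or good (60 points or more) over all patients. The Sample size section plans on that rate, assuming that it "would be 78% for microfracture surgery and 97% for autologous, cell-derived, tissue-engineered cartilage transplantation", with alpha "0.05 (two-sided), and power = 80"%. It arrives at 84 patients, then 50 per group for 20% dropout.

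Under Statistical analysis, the only test assigned to such a rate is unadjusted: "Pearson’s chi-squared test or Fisher’s exact test will be used for intergroup comparisons of categorical variables, such as curative outcomes". A logistic model follows, to adjust for possible confounders. Its examples are "age, sex, etiology, cartilage defect area, meniscus injury, course of disease, severity of cartilage injury, postoperative complications, and surgeon (experience". The article does not say whether this model is primary or supportive.

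Secondary outcome measures lists a baseline Lysholm assessment, so the pre-treatment value of the primary measure will be available. It is not named in either analysis. The analysis set is intent-to-treat, with the last observation carried forward for patients lost to follow-up.

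**The concern.** The pre-treatment value of an outcome is usually among its better predictors. The eligibility criteria set no limit on baseline Lysholm, so patients may enter anywhere on the scale, including already at 60 or above. If the baseline score predicts who ends above 60, a comparison that ignores it leaves explainable variation in the result. The trial is planned for only 80% power, and the information needed to do better is collected anyway.

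The covariates that are named do not fill the gap. They include one measured after randomisation (postoperative complications) but not the baseline score. At stake is the chance of detecting the planned difference, not the validity of the test.

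**Working it through.** **Inputs from the article.** Success rates 78% and 97%; two-sided alpha 0.05; target power 80%; 84 evaluable patients; 50 per arm randomised ("100 eligible patients will be randomly assigned to receive autologous-cell-derived tissue-engineered cartilage grafts" or microfracture).

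**Assumed input.** The correlation rho between baseline and 12-month score on a latent normal scale. The article gives none; 0.3, 0.5 and 0.7 are shown.

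**1. The plan's own figure.** The pooled two-proportion formula, with mean rate (0.78 + 0.97)/2 = 0.875, is

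n per arm = [1.96 × √(2 × 0.875 × 0.125) + 0.8416 × √(0.78 × 0.22 + 0.97 × 0.03)]² / 0.19²
= [0.9167 + 0.3770]² / 0.0361 = 46.4, so 47 per arm and 94 in total.

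The stated 84 is not reproduced. Other two-sided versions give 80 (arcsine), 88 (unpooled) and 114 (continuity-corrected). A likelihood-ratio formula comes closest, with 79.3% power at 84. This is a separate matter; the comparison below uses the planned 50 per arm.

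**2. Power of the named tests at 50 per arm.** Exact power is the sum, over all pairs of success counts (i, j), of Bin(i; 50, 0.78) × Bin(j; 50, 0.97) for the pairs that reject.

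| Test | Exact power |
|---|---|
| Pearson, uncorrected | 88.0% |
| Fisher | 77.4% |
| Fisher if an expected count is below 5, otherwise Pearson | 85.6% |

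The third row is an assumed rule; the article states none. Under it, Fisher is used in about 17% of trials.

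**3. Adjusting for baseline alone.** Draw baseline x and error e as standard normal. Success is μ + rho·x + √(1 − rho²)·e > 0, with μ set in each arm to give 78% or 97%. Treatment is tested by the score test in a logistic model containing x. Two simulations, of 4000 and 5000 runs per setting, gave:

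| rho | Adjusted power | Difference from Pearson's 88.0% |
|---|---|---|
| 0.3 | 88.3% and 88.5% | +0.3 and +0.5 |
| 0.5 | 90.8% and 90.5% | +2.8 and +2.5 |
| 0.7 | 94.5% and 94.1% | +6.5 and +6.1 |

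A likelihood-ratio version reached 91.2% at rho 0.5 (Pearson in the same runs 87.6%) and 95.8% at 0.7 (88.9%). Part of that difference comes from the test: the unadjusted likelihood-ratio test had 88.8% and 90.1%. In a re-run at 50 per arm, the type I error of the baseline-adjusted score test was 4.9% to 5.7%.

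**4. Limits of the model.** Expected failures: 50 × 0.22 + 50 × 0.03 = 11 + 1.5 = 12.5. Nine covariates would leave 12.5/9, or about 1.4 failures each. In simulations at 42 per arm with the nine covariates as pure noise (1000 runs), adding baseline gained nothing: 80.6% without and 80.4% with it at rho 0.3, 79.7% and 79.0% at rho 0.5. Type I error was about 8% without baseline and 10% with it. The probability of no failures in the experimental arm is 0.97^50 = 0.218, or about 22%; the maximum-likelihood log odds ratio is then infinite.

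**The case against.** The strongest reply is that this is a preference about efficiency. The unadjusted test is valid, and its error rate already allows for chance baseline imbalance. If Pearson's test is used, power at 50 per arm is 88.0%, above the 80% target. The covariate list is introduced as examples, and a full analysis plan that is not shown may add baseline. At weak correlation nothing is gained. These points stand. They rule out saying that baseline is definitely omitted, or that power is certainly lost. They do not change the fact that the one test assigned to the primary rate carries no covariate.

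A reader might infer three stronger things that the article does not support:

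- **A gain from about 70% to 83%.** This comes from 40 patients per arm, rho 0.5 and the assumed Fisher fallback. The stated analysis set keeps withdrawn patients and imputes their values, so the planned number is about 50 per arm. Even at 40 per arm, Pearson's exact power is 81.1% against about 83% adjusted, so nearly all of that gain comes from avoiding Fisher.
- **Adjustment without any cost.** With no failures in one arm in about 22% of trials, a fallback must be planned.
- **Baseline imbalance as bias.** The article describes a computer-generated sequence and no stratification, but the comparison is still randomised.

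**Conclusion.** The point holds as a moderate matter of efficiency. The planned primary comparison is unadjusted although the baseline value of the outcome is collected. The benefit of adjusting for it alone is nil to small for correlations up to 0.5 and more useful at 0.7. These figures rest on the plan's own rates, 50 analysed per arm, a latent normal model and correlations that are assumed.

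Any gain beyond this comes from avoiding Fisher's test. The 10.6-point gap between the two named tests (88.0 − 77.4) exceeds the baseline gain at every correlation examined. Leaving the choice between them open therefore matters at least as much. Nothing here suggests that the planned test would give a biased answer.

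**What to change.** - Make the primary comparison of the 12-month efficacy rate a logistic model with treatment and continuous baseline Lysholm only. Test treatment by the score or likelihood-ratio test, naming one. Report the baseline-standardised difference in rates with its 95% CI.
- State in advance that a penalised fit will be used if an arm has no failures.
- Keep the unadjusted comparison as a sensitivity analysis, and fix beforehand whether it is Pearson's or Fisher's test, or the rule for choosing.
- Label the many-covariate logistic model as supportive. Do not simply add baseline Lysholm to its nine items: with about 12 failures expected, that model is already overloaded.

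The cost is a few sentences of analysis text. No patients, visits or measurements are added. The small downside is the extra method needed when an arm has no failures.
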